## Introduction

There are growing numbers of children with complex health conditions who are dependent on medical technologies to maintain their health, and gastrostomy (or enteral) feeding is one such technology. The authors’ own analyses of inpatient hospital (Hospital Episodes Statistics, HES) data found that among children with life-limiting conditions (LLC)^1^ in England, the number having permanent gastrostomy surgery each year has risen from 183 in 2000/2001 to 1004 in 2014/2015. In 2014/2015, the total number of children with an LLC, aged 0–19 in England, who have ever had a gastrostomy was 10 154. This is much higher than published estimates of ~430 children.^2^

Children requiring some or all of their nutrition via gastrostomy tubes have a wide range of underlying diagnoses, including neurodisability, inherited metabolic diseases, congenital cardiac conditions, cystic fibrosis, gastrointestinal diseases and cancer.

At present, in the UK, the recommended feed for children on enteral feeding is commercially produced complete liquid nutrition (formula), prescribed by the child’s dietitian.^3^ However, there is a growing body of parents who are interested in and/or choosing to feed their children meals they have prepared themselves which are then liquidised so they can be administered via a gastrostomy (referred to forthwith as ‘home-blended foods’).^4–6^ Parents choosing to use home-blended foods have reported benefits such as improved gastro-oesophageal reflux, less constipation and less distress in their child.^7^ There are also perceived psychosocial benefits: it may fulfil parents’ need to nurture, and the child is not excluded from sharing the same food as the rest of the family. Prescribed formula, in contrast, is regarded as a medical product rather than food.^6^

Limited research evidence^8^ and reports from clinicians suggest that the long-term use of gastrostomy feeds for children with complex health conditions can result in complications including progressive feed intolerance/gut failure.^8^ There are suggestions that a home-blended diet may reduce the risk of gut failure but there is currently no evidence to support this.

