Recent national surveys of paediatric dietitians in the UK^4^ and the USA^5^ both found that more than half of respondents would recommend the use of a home-blended diet (56% and 58%, respectively). In the UK, however, that recommendation was to use home-blended food as a supplement to formula feeds rather than their exclusive use.

At the same time, concerns have been raised by professional organisations, including the European Society for Paediatric Gastroenterology Hepatology and Nutrition and British Dietetic Association, about the risks associated with a diet of home-blended foods. These include: nutritional inadequacy, microbial contamination and blockage of the gastrostomy tube. Policy/position statements from such organisations do not recommend that children (or adults) are fed home-blended foods through their gastrostomy tubes.^9^ Importantly, it was acknowledged in these guidelines that the evidence for this statement is low and further research is likely to have an impact on this recommendation.

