#### Data collection

Data will be collected at three time points: at baseline and then at 9 and 18 months. At each time point, data on a range of outcomes as well as relevant clinical and feeding information will be collected from parents/children/young people and clinicians. See table 2 for summary of proposed outcomes and data sources (these are subject to change following WS1).

**Table 2 T2:** Proposed variables and data sources for WS2

Variable	Type of variable	Proposed measure	Source	Timings of data collection (months)		
				0	9	18
Participant characteristics/predictors						
Age	Predictor	Date of birth	Parent	√		
Ethnicity		Census groups	Parent	√		
Deprivation		Index of Multiple Deprivation (based on postcode)	Parent	√	√	√
Parental educational attainment		Census groups	Parent	√		
Household composition		Number of children, marital/living status	Parent	√	√	√
Diagnosis			Paediatrician	√		
Comorbidities			Paediatrician	√	√	√
All medications			Paediatrician	√	√	√
Complexity		Disability Complexity Scale^23 24^	Paediatrician	√	√	√
Length of time gastrostomy fed at T0		Months/years	Parent	√		
Comparator						
Diet: formula/blended	Main grouping variable		Parent	√	√	√
Outcomes						
Nutritional content of feeds	Outcome	Commercial for formula	Dietitian/parent	√	√	√
		myfood24^15^	Parent	√	√	√
Anthropometric data	Outcome	Height or length Weight Triceps skinfold thickness or mid-arm circumference	Dietician Paediatrician	√	√	√
Gastrointestinal symptoms	Outcome	PedsQL gastrointestinal^19^	Parent/child	√	√	√
Child quality of life	Outcome	PedsQL generic module^18^	Parent/child	√	√	√
Parental quality of life	Outcome	EQ-5D-5L^25^ Parenting Morale Index^26^	Parent	√	√	√
Healthcare use	Outcome	Client service receipt inventory^27^	Parent	√	√	√
	Outcome	Number of hospital admissions Number of accident and emergency (A&E) attendances	HES data	√	√	√
Safety	Outcome	Tube blockages Number of stoma infections Number of gastrointestinal infections	Parent			
	Outcome	Number of hospital admissions and A&E attendance associated with child’s gastrostomy/diet	HES and parent	√	√	√
Family resource use	Outcome	Time preparing feeds; impact on other caring/parenting Financial costs	Parent	√	√	√
Non-staff NHS resource use	Outcome	Cost of formula and packaging Dietetic resources	Dietitian	√	√	√

EQ-5D-5L, 5-level version of EuroQol-5 Dimension; HES, Hospital Episodes Statistics; NHS, National Health Service; PedsQL, Pediatric Quality of Life Inventory; WS2, workstream 2.

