The PedsQL generic scale^18^ and PedsQL gastrointestinal symptoms module^19^ will be scored as per the guidelines and transformed to a score of 0–100.The height (or length) and weight will be used to calculate an age and sex-adjusted body mass index (BMI SD score (SDS)).The myfood24 data programme analyses the nutritional content of the home-blended diet and will compute the calorie intake and the macro/micronutrient content of the feed and any oral feeds. The same data for the formula fed group will have been obtained, via the dietitian, from the commercial supplier.The parent-reported number of site infections and other tube-related complications will be reported as total counts for each child.The diagnostic (International Classification of Diseases, Tenth Revision)^20^ and procedural codes (OPCS Classification of Interventions and Procedures) in the HES data will be used to identify admissions which were related to complications of the gastrostomy tubes or infections. The number of admissions and A&E attendances will be calculated for each child. Length of stay for each admission will also be calculated for the resource use analyses.Parent QoL. The EuroQol-5 Dimension (EQ-5D) visual analogue scale is scored 0–100 and the five-component scale of the 5-level version of EuroQol-5 Dimension (EQ-5D-5L) will be converted to a single score using a UK-specific value set.^21^ The 10-item Parenting Morale Index is scored from 0 to 100.

For all outcomes we will report the baseline score, follow-up scores and change score.

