#### Assessing safety (objective 2) and benefits (objective 3)

The safety and benefits of blended diet compared with formula diet will be assessed using multivariable regression analyses. The type of regression will depend on the outcome of interest: logistic (tube blockage, appropriate nutritional content; yes/no), linear (PedsQL gastrointestinal module score, BMI SDS or upper arm circumference, calories, Parenting Moral Index (PMI), EQ-5D), Poisson or negative binomial (number of A&E or hospital admissions for infections or complications of gastrostomy tube). Each analysis will account for the multiple confounding factors in this population (age, underlying diagnoses, comorbidities, outpatient attendance, parental factors, socioeconomic status) and the main covariate of interest will be feeding status (blended vs formula). Study site will be added as a random effect to the models to allow for site-level variation. Estimates and 95% CIs will be reported from the regression model for each outcome measure.

The flow of participants through the study will be detailed including the number of individuals contributing to each analysis. The amount of missing data will be summarised for each outcome measure and multiple imputation will be used to assess the robustness of the results. Results will be compared with the complete case analyses and important differences discussed. Sensitivity analyses will be considered to explore departures from the missing at random assumption.

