#### Long-term follow up (objective 5)

The utility of routine data sources as an option for long-term follow-up of study participants will be assessed by examining the concordance between parent-reported data on A&E visits and hospital admissions due to infections or complications of their gastrostomy tube with HES data for the corresponding time period. Concordance will be assessed using the kappa statistic both for the total sample and separately by the home-blended and formula fed groups.

If there is concordance between the parental reported infection and gastrostomy-related healthcare usage and HES data, long-term follow-up would be possible by obtaining further extracts of HES data and ONS death certificate data. The HES data will provide future information on admissions and A&E visits due to infections and complications of the gastrostomy (blockages, revisions, replacements). The ONS data will provide date and cause(s) of death if the child has died.

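### Table 2 counts hospital events linked to gastrostomy or diet as safety outcomes, but the derivation rule, count model and long-term plan keep only infections and gastrostomy or tube complications

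*Protocol article*

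**What the plan says.** Four places in the protocol article set out the hospital safety outcome.

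- **Data collection, Table 2, Safety row:** "Number of hospital admissions and A&E attendance associated with child’s gastrostomy/diet", from HES and parents, at months 0, 9 and 18.
- **Data analyses (scoring of outcomes):** diagnosis and procedure codes in HES "will be used to identify admissions which were related to complications of the gastrostomy tubes or infections".
- **Assessing safety (objective 2) and benefits (objective 3):** the Poisson or negative binomial model is for "number of A&E or hospital admissions for infections or complications of gastrostomy tube".
- **Long-term follow up (objective 5):** agreement between parent report and HES is assessed for infections and gastrostomy complications. Future extracts are said to supply "admissions and A&E visits due to infections and complications of the gastrostomy (blockages, revisions, replacements". For deaths, "The ONS data will provide date and cause(s) of death if the child has died".

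Table 2 also lists, as healthcare use and not as safety, "Number of hospital admissions Number of accident and emergency (A&E) attendances" from HES with no restriction on cause.

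The Introduction gives the background. On professional concerns about home-blended food it says "These include: nutritional inadequacy, microbial contamination and blockage of the gastrostomy tube". On long-term gastrostomy feeding in general it says this "can result in complications including progressive feed intolerance/gut failure", and it adds that a blended diet has been suggested to lower the risk of gut failure, so far without evidence.

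**The concern.** Table 2 promises a safety outcome with two parts, gastrostomy and diet. The sections that turn it into data, a model and a long-term extract mention only infections and gastrostomy or tube complications. An analyst who follows those sections will build a narrower outcome than Table 2 describes.

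The missing part bears on the research question. An admission for malnutrition or for feed intolerance is neither an infection nor, on a plain reading, a tube complication. Nutritional inadequacy is one of the concerns the Introduction lists about home-blended food, and gut failure is an outcome on which blended food might do better. Leaving such admissions out could hide a harm or a benefit. The model's result could be reported as similar safety-related admissions on the two diets when the admissions most directly tied to diet had not been counted.

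The same restriction applies to the concordance check, which decides whether routine data can support follow-up over 10 years or more.

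**Working it through.** **Causes counted, place by place.** The plan gives no figure for this outcome, so the main check compares the passages.

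- Table 2, Safety row: gastrostomy-related yes; diet-related yes.
- HES derivation rule: tube complications and infections yes; other diet-related causes not named.
- Count model: the same two causes; other diet-related causes not named.
- Concordance check: infections and gastrostomy complications; other diet-related causes not named.
- Long-term events: the same, with blockages, revisions and replacements as examples, plus deaths; other non-fatal diet-related causes not named.

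The long-term wording refers to the gastrostomy and not only the tube, which is slightly wider, but its examples are all mechanical.

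**Whether other outcomes fill the gap.**

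- *Nutritional content and calories* describe intake at months 0, 9 and 18. They do not count hospital events caused by poor intake or intolerance.
- *BMI SDS or arm circumference* and the *PedsQL gastrointestinal score* show growth and symptoms at the same three points, not serious episodes between them.
- *All-cause HES admissions and A&E attendances* would include the events, mixed with admissions for underlying disease, so a diet-related difference would be diluted.
- *Mortality and adverse event rates* are to be reported by diet in the cost-consequences section, but the article does not define an adverse event.
- *Long term:* of the first three groups, only HES admissions could continue through routine data. Intake, anthropometry and questionnaire scores could not.

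**How much a narrow count can hide (illustration; all inputs assumed).** Let s be the share of formula-group gastrostomy- or diet-related admissions that falls outside the infection and tube codes. Let the blended-to-formula rate ratio be 1.0 inside those codes and r outside. The rate ratio for the Table 2 outcome is then

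(1 − s) × 1.0 + s × r.

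- r = 2.0: s = 10%, 20%, 30%, 50% gives 0.9 + 0.2 = 1.1; 0.8 + 0.4 = 1.2; 0.7 + 0.6 = 1.3; 0.5 + 1.0 = 1.5.
- r = 0.5: the same shares give 0.9 + 0.05 = 0.95; 0.8 + 0.10 = 0.90; 0.7 + 0.15 = 0.85; 0.5 + 0.25 = 0.75.

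In every case the narrow count shows 1.0. This shows how the narrow count works, in both directions. It does not estimate what this cohort will show.

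**The case against.** The best case for the plan has four parts.

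1. **Table 2 does include diet-related events.** A reader might infer that the study excludes them from safety altogether during the 18 months. The documents do not support that: the Safety row includes them at every time point, from parents as well as HES, and the code rule describes only the HES source. The documents conflict; they do not settle on exclusion. This stands, and it sets the limits of the point.

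2. **The main concerns are otherwise covered.** A reader might infer that the plan ignores the principal risks of blended food. It does not. Of the three concerns listed, microbial contamination and tube blockage fall within the narrow rule, and nutritional adequacy, calories and growth are modelled under the safety and benefit heading. Gut failure is attributed to long-term gastrostomy feeding generally and is presented as something a blended diet might reduce. All of this stands. What remains is that these measures replace a count of diet-related hospital events only in part.

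3. **Details belong elsewhere.** The code list can sit in the statistical analysis plan, the model's bracketed outcomes may not be exhaustive, and Table 2 may change after Workstream 1. All fair. But the article already fixes which causes count, and does so differently in different sections. That is more than missing detail.

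4. **Objective 5 is about feasibility.** Further HES extracts could hold any code, so gut failure need not be lost. This stands in part: the extract is not limited in so many words. However, the concordance check would test only infections and gastrostomy complications, so routine data would not have been checked for diet-related events.

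A reader might also infer from Table 2's short label for diet that a child's loss of gastrostomy feeding would go unrecorded. The questionnaires and clinician forms are not shown, so this cannot be concluded.

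**Conclusion.** The point holds as an internal inconsistency with a practical consequence. If the derivation, model and long-term sections are followed literally, diet-related admissions drop out of the modelled safety count, the concordance check and the stated long-term events, although Table 2 includes them. The long-term part is the more serious, because fewer other measures are available there.

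Its size in this study is unknown: the article gives no rate for any hospital event. The conclusion rests on two readings: that the diet part of Table 2's wording covers admissions for nutritional harm or feed intolerance, and that the cause lists in the later sections are meant as definitions. It does not depend on any assumed event rate. It should be corrected before the analysis plan is signed off. It does not invalidate the design.

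**What to change.** Reconcile the scoring rule, the count model and the long-term section with Table 2:

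- Prespecify a second HES category, diet-related (nutrition or feed-tolerance) admissions, with its diagnosis and procedure codes listed in the statistical analysis plan.
- Model it alongside the infection and tube-complication count and report the two separately.
- Include it in the parent-versus-HES concordance check. Table 2 already names parents as a source for gastrostomy- or diet-associated events.
- Name it among the events for the long-term extract.

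Narrowing Table 2 to match the other sections would also restore consistency, but it would give up the diet-related events.

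The cost is a longer code list on HES data already due to be linked, one more count model and one more set of kappa statistics. There are two drawbacks. Some of these admissions will reflect underlying disease, and in a non-randomised cohort adjustment may not remove that; this is why the category should stay separate. The counts may also be small: at the planned ratio, 300 × 1/3 = 100 children are on a blended diet and 300 × 2/3 = 200 on formula, so the estimate may be imprecise and should be read from its confidence interval.

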#### Assessing safety (objective 2) and benefits (objective 3)

The safety and benefits of blended diet compared with formula diet will be assessed using multivariable regression analyses. The type of regression will depend on the outcome of interest: logistic (tube blockage, appropriate nutritional content; yes/no), linear (PedsQL gastrointestinal module score, BMI SDS or upper arm circumference, calories, Parenting Moral Index (PMI), EQ-5D), Poisson or negative binomial (number of A&E or hospital admissions for infections or complications of gastrostomy tube). Each analysis will account for the multiple confounding factors in this population (age, underlying diagnoses, comorbidities, outpatient attendance, parental factors, socioeconomic status) and the main covariate of interest will be feeding status (blended vs formula). Study site will be added as a random effect to the models to allow for site-level variation. Estimates and 95% CIs will be reported from the regression model for each outcome measure.

The flow of participants through the study will be detailed including the number of individuals contributing to each analysis. The amount of missing data will be summarised for each outcome measure and multiple imputation will be used to assess the robustness of the results. Results will be compared with the complete case analyses and important differences discussed. Sensitivity analyses will be considered to explore departures from the missing at random assumption.

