#### Sample size

Given that no data are available on the exact proportion of children who receive formula feeds versus a home-blended diet in England, various scenarios were explored to ensure that the study would be adequately powered. A sample size of 300 for the analysis (assuming there are twice as many formula fed as home blended) should enable us to estimate proportions within each group to within a margin of error of ≤10% and continuous measures (eg, Pediatric Quality of Life Inventory (PedsQL) assuming SD 20) to within an SE of 4 points.

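### Tube-related complications are aggregated as counts per child, but tube blockage is modelled only as yes/no, and parent-reported infection counts are matched to no named model

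*Protocol article*

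**What the plan says.** Three parts of the article bear on how tube complications are analysed.

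- **Data analyses.** In a list of the scoring and aggregation needed before modelling, it states: "The parent-reported number of site infections and other tube-related complications will be reported as total counts for each child".
- **Assessing safety (objective 2) and benefits (objective 3).** Outcomes are assigned to model types. Blockage falls under "logistic (tube blockage, appropriate nutritional content; yes/no". The count models are "Poisson or negative binomial (number of A&E or hospital admissions for infections or complications of gastrostomy tube". The same section says in general terms that safety will be assessed by multivariable regression, and adds: "Estimates and 95% CIs will be reported from the regression model for each outcome measure".
- **Table 2.** The parent-reported safety outcomes are tube blockages, stoma infections and gastrointestinal infections. The two infection items are labelled as numbers; the blockage item is not.

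The section on long-term follow-up (objective 5) lists blockages, with revisions and replacements, as complications of the gastrostomy. The Introduction names the professional bodies' concerns about home-blended diets as "nutritional inadequacy, microbial contamination and blockage of the gastrostomy tube".

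**The concern.** Read together, these parts do not agree on what the blockage outcome is. If blockage is a tube-related complication, as the long-term follow-up section treats it, the data analyses section makes it a count, and the safety section then reduces that count to any/none. A child with one blockage and a child with six are scored alike. If blockage recurs, most children in both groups score yes and the comparison flattens.

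The infection counts have a different gap. Infections that lead to no admission or A&E visit fall outside the only count model named, yet they are the listed outcomes closest to the contamination concern.

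Blockage and contamination are two of the three risks that the Introduction gives, so this touches the core of objective 2. A related question is the denominator: the totals are described without reference to the time over which each child was observed.

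**Working it through.** **Inputs from the article.** "A sample size of 300 for the analysis (assuming there are twice as many formula fed as home blended", taken as 100 home-blended and 200 formula-fed children; 95% confidence intervals; data at 0, 9 and 18 months.

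**Assumed, because the article gives no figure.** Mean blockages per formula-fed child (μ0, from 0.1 to 2), rate ratio 1.5 (so μ1 = 1.5 μ0), negative binomial dispersion k = 1 (varied from 0 to 2), and dropout. The comparison is unadjusted and ignores the site effect.

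**Step 1: the plan's own figures.** For a proportion of 0.5, 1.96 × √(0.25/100) = 9.8% in the blended group and 1.96 × √(0.25/200) = 6.9% in the formula group, so the aim to "estimate proportions within each group to within a margin of error of ≤10" per cent is reproduced. For the continuous measure ("assuming SD 20) to within an SE of 4 points"), 20/√100 = 2.0 is the standard error and 1.96 × 2.0 = 3.92 is the 95% half-width. The 4 points therefore reproduce as a margin of error, not as an SE; this is a side remark. No power is claimed for any comparison.

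**Step 2: formulas.**
- Probability of any event: P = 1 − (1 + kμ)^(−1/k).
- Yes/no analysis: variance of the log odds ratio = 1/[100 P1(1 − P1)] + 1/[200 P0(1 − P0)].
- Count analysis: variance of the log rate ratio = (1/μ1 + k)/100 + (1/μ0 + k)/200.
- Power = Φ(|effect|/SE − 1.96).

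**Step 3: one case in full (μ0 = 1, k = 1).** P0 = 1 − 1/2 = 0.50 and P1 = 1 − 1/2.5 = 0.60. The odds ratio is (0.60/0.40)/(0.50/0.50) = 1.5, the same as the rate ratio, so the two standard errors compare directly.
- Yes/no: SE = √(1/24 + 1/50) = 0.248; 0.405/0.248 = 1.63; power = Φ(−0.33) = 37%.
- Count: SE = √(1.667/100 + 2/200) = 0.163; 0.405/0.163 = 2.48; power = Φ(0.52) = 70%.

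In terms of precision, an estimate of 1.5 would carry a 95% interval of about 0.92 to 2.44 from the yes/no model and 1.09 to 2.07 from the count model.

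**Step 4: range (rate ratio 1.5).** Efficiency is the squared effect/SE for yes/no divided by that for the count.

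| Mean per formula-fed child | Power, yes/no (k = 1) | Power, count (k = 1) | Efficiency of yes/no, k from 0 to 2 |
|---|---|---|---|
| 0.1 | 18% | 20% | 85–93% |
| 0.2 | 27% | 32% | 74–87% |
| 0.5 | 36% | 54% | 55–69% |
| 1 | 37% | 70% | 41–45% |
| 2 | 31% | 80% | 17–28% |

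**Step 5: unscaled totals.** Suppose the true rate ratio is 1, dropouts are observed for 9 of 18 months, and their partial totals are used as they stand. The apparent ratio is (1 − 0.5 d1)/(1 − 0.5 d0), where d1 is dropout in the blended group and d0 in the formula group.
- 20% and 20%: 0.90/0.90 = 1.00.
- 10% and 20%: 0.95/0.90 = 1.06.
- 10% and 30%: 0.95/0.85 = 1.12.
- 30% and 10%: 0.85/0.95 = 0.89.

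**The case against.** Four stronger readings are tempting, and the article does not support them.

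- **That infections get no adjusted analysis.** The safety section promises multivariable regression for safety and an estimate for each outcome measure. The infections are unassigned, not excluded, and a SAP could complete the mapping. Table 2 is also open to change after WS1.
- **That the safety comparison loses much of its power.** No blockage rate, dispersion or effect size is given. At a mean of 0.1 the loss is 2 percentage points. The sample size rests on precision, partly for proportions, with which a yes/no outcome is consistent. No outcome is named as the main safety comparison. The calculation also generates data from the model it favours.
- **That the comparison is biased by dropout.** This needs follow-up time that differs by diet and a rule that partial totals are summed as if complete, which the article does not state. It says that baseline, follow-up and change scores will be reported for all outcomes, and it plans multiple imputation, a comparison with complete cases and consideration of departures from missing at random. Even the direction of any bias is unknown. An offset is a detail that an article commonly leaves to the SAP.
- **That blockage is certainly collected as a count.** Table 2 does not label it as a number. The count follows from the data analyses section together with the long-term follow-up section.

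It is also fair to say that whether a child had any blockage is a legitimate question.

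What stands is narrower. The article does fix the blockage model, so the conflict with its own aggregation rule is not simply something left to the SAP. Lower efficiency also widens the confidence intervals that the article promises, whether or not power was claimed.

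**Conclusion.** The point holds in a limited form. The article aggregates tube-related complications as counts but models blockage only as yes/no, and it names no model for the parent-reported stoma and gastrointestinal infection counts. At a rate ratio of 1.5 and dispersion 1, the power lost by dichotomising runs from 2 percentage points at a mean of 0.1 per child (18% against 20%), through 18 at 0.5 and 33 at 1, to 49 at a mean of 2 (31% against 80%). All of this rests on assumed rates, effect and dispersion and on an unadjusted comparison. In every setting tabulated the count analysis was at least as efficient, so the choice favours the count even with the rate unknown. The follow-up issue is secondary and conditional: under the 9-of-18-month assumption, a dropout difference of 10 to 20 percentage points moves a true ratio of 1 by about 5 to 12% in either direction, and equal dropout does not move it.

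**What to change.** Reconcile Table 2, the data analyses section and the safety section, and carry the result into the SAP.

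1. State in Table 2 that the number of tube blockages is recorded, as for the infections.
2. Model parent-reported blockages, stoma infections and gastrointestinal infections as counts by negative binomial regression, with the confounders and random site effect already planned.
3. Use the log of the period covered by each family's returned questionnaires as the offset. Keep the planned multiple imputation as the robustness check.
4. For HES admissions and A&E attendances use a separate offset: the linkage period, ended at death or withdrawal of linkage consent. These counts do not depend on questionnaire return, so a questionnaire-based denominator would inflate the rates of families who did not respond.
5. Keep any/none blockage as a secondary summary.

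The cost is revised wording, slightly more analysis work, and reliance on parents' recall of how many events occurred rather than only whether one did.
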